### Study setting

Patients with OUD availing the outpatient/inpatient clinical services under the Centre for Addiction Medicine, Department of Psychiatry, National Institute of Mental Health and Neuro-sciences (NIMHANS), Bengaluru, India will be approached. The course of the trial, its benefits, possible demerits, voluntary participation with a choice to quit the study at any time will be explained in simple comprehensible language. Patients satisfying the inclusion criteria will be requested to provide written informed consent. Consecutive consenting patients will be randomly assigned to one of the two groups − Standard treatment + Yoga-based intervention (YAT), or waitlist group-standard treatment (TAU) alone by the biostatistician. Allocation sequence will be generated by biostatistician using computer-generated random numbers and allocation concealment will be done using opaque sealed envelopes. A validated and standardized yoga program for OUD will be used as an intervention. Although double blinding will not be possible in the study, the clinicians treating the subjects, the outcome assessors, and data analysts will remain blind to the subject-group allocation status throughout the period of the study. All participants will be continuing their routine standard care (OST/MOUD and psycho-social support) till the study concludes. Figure 1 provides the study design outline.

Buprenorphine/naloxone dosage will be recorded at the beginning of yoga intervention; dosage will be adjusted based on the clinical presentation of the patient by the treating psychiatrist.

### Selection of participants

#### Inclusion criteria

Diagnosis of OUD (DSM 5 criteria)Score >3 on Clinical Global Impression − Severity (CGI-S)Age range: 18–50 yearsAll genderWritten informed consentAccess to smartphone and internet

#### Exclusion criteria

Prescription of OST other than buprenorphine/naloxoneSevere withdrawal symptoms (COWS>25)Other diseases causing intractable painPrescription opioids for pain related to other medical conditionsCo-morbid alcohol/benzodiazepine/cannabis/multiple substance dependence in last six months except for nicotineImpaired intellectual functioning (HMSE>24)MRI contraindications such as claustrophobia, metal implants or paramagnetic objects in the bodyNeurosurgery/loss of consciousness due to head injury in the past/diseases affecting CNSSevere psychiatric or medical illness preventing practice of the yoga programPregnancy or post-partumRisk of harm to self or othersCurrent/ recent practice of yoga/meditation (>4hr/month in last three months)

### Clinical assessment

The demographic and clinical information will be collected using structured scales and proforma. Diagnosis of OUD will be made as per Diagnostic and Statistical Manual of Mental Disorders (DSM 5) criteria and participants will be screened using Diagnostic Interview for Anxiety, Mood, and OCD and Related Neuropsychiatric Disorders (DIAMOND)^54^. The clinical diagnosis would also be confirmed independently by a qualified psychiatrist. Pain and Craving will be assessed by Brief Pain Inventory (BPI) and Opioid Craving Scale (OCS), respectively. Withdrawal symptoms will be assessed by Clinical Opiate Withdrawal Scale (COWS). The Time-Line Follow Back (TLFB) method will be employed at the three- and six-month intervals to quantify self-reported frequency of opioid use and maximum weeks of abstinence. The TLFB is a reliable and valid tool in assessing self-reported drug use and leverages a calendar and significant events to aid participants in recalling their substance use patterns, thereby offering a comprehensive view of consumption trends over time^55^. Perceived stress will be assessed using the perceived stress scale (PSS). Work and social life will be rated on the Work and Social Adjustment Scale (WSAS) and Quality of Sleep on Pittsburg Quality of Sleep Index (PSQI). Adverse effects of opioid substitution therapy (buprenorphine/naloxone) will be assessed using the Udvalg for Kliniske Undersogelser (UKU) Side Effects Rating Scale.

In addition, traditional diagnoses related to yoga therapy will be determined at baseline using the Vedic Personality Inventory and Ayu-Soft Prakriti Diagnostic Tool. Table 1 provides the schedule of assessment.

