## Objectives

### Primary objectives

To evaluate the effect of a six-month add-on yoga-based intervention on opioid abstinence (opioid-negative urine results and negative self-reported frequency of opioid use since last follow-up), pain and craving in patients with OUD as compared to standard treatment alone.To examine the neurobiological underpinnings of yoga in OUD by estimating plasma beta-endorphins and brain hemodynamics in response to opioid-use-related visual cues, the stop signal task and resting state functional connectivity through fMRI.

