#### Primary outcome measures

Key measures include opioid abstinence confirmed by negative urine screening and self-report, levels of pain measured by BPI, the intensity of craving tracked by OCS, beta-endorphin levels, and fMRI-BOLD responses to tasks (stop signal, visual cue craving) and resting state functional connectivity through fMRI.

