#### Secondary outcome measures

These include percentage of participants maintaining abstinence, the longest duration of continuous abstinence, withdrawal symptoms (COWS), severity (CGI), pain threshold (algometer), cognitive performance (n-back task and Stroop task), stress levels (PSS), quality of sleep (PSQI), functioning (WSAS), HRV, cortisol levels, brain GABA levels through MRS, buprenorphine dosage during withdrawal and maintenance phases, side effects (UKU), and gunas (VPI).

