#### Description of some major assessments

**Urine screening for opiods:** Urine screening for opioids is considered as a gold standard for monitoring abstinence. Test depending on the Immunoassay method will be used. It will be done using the opioid strip test which is a rapid, easy and reliable test that is routinely used in clinical settings in India.**Brief Pain Inventory**^57^: It is a reliable and valid tool to assess pain. The scale measures pain intensity, pain severity and pain interference. It has good internal consistency (Cronbach’s alpha = 0.87). The scale is rated by the patient, has 16 items, and provides details regarding pain in the last 24 hours.**Opioid craving scale**^58^: It is a three-item test that is a reliable and valid tool to assess craving in opioid use disorders^59^ and has been used in many studies before. It has good internal consistency (omega = 0.81). Each item is rated by the patient on a visual analog scale from 0–10.**Plasma beta-endorphin estimation:** A blood sample will be collected around 9 am after overnight fasting. 10ml of blood will be drawn and collected into chilled EDTA (1ml/ml of blood) tubes containing aprotinin (500 KIU/ml). The sample will be centrifuged at 1600 × g for 15 minutes at 2 − 8°C. The plasma sample will be immediately frozen and kept at -80°C till analysis. Plasma beta-endorphin levels will be measured using MILLIPLEX MAP multiplex assay kit (Millipore Life sciences, MA), and analyzed by LUMINEX xMAP technology. (CV=6.25%).**Serum Cortisol estimation:** Venous blood (around 5 ml) will be collected from patients in anticoagulant-free tubes around 9 am and serum will be separated after 30 minutes by centrifugation (2900 rpm for 15 minutes). Coded serum sample will be stored at -80°C. The serum cortisol levels will be measured using Enzyme-linked Immuno-Sorbent Assay (ELISA) by commercial reagents according to the manufacturer’s instructions.

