**Clinical Assessment**				
DSM-5 Clinical Interview Diagnosis	✓			
DIAMOND	✓			
Urine Toxicology for Opiods (monthly)	✓	✓	✓	✓
Self-reported Opioid Use Frequency (TLFB)	✓	✓	✓	✓
Maximum Consecutive Abstinence Weeks (TLFB)	✓		✓	✓

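### Longest continuous abstinence has self-report as its only named source, although the trial defines abstinence by urine and self-report together

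*Protocol article*

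**What the plan says.** Three places in the protocol article describe the duration outcome:

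- **Secondary outcome measures** lists "the longest duration of continuous abstinence" with no condition on urine.
- **Clinical assessment** assigns it to the TLFB, used at three and six months "to quantify self-reported frequency of opioid use and maximum weeks of abstinence". The same paragraph describes the TLFB as a tool for self-reported drug use.
- **Table 1** labels the row "Maximum Consecutive Abstinence Weeks (TLFB") and keeps a separate row for "Urine Toxicology for Opiods (monthly").

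Three other places say what abstinence means in this trial:

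- **Primary objectives:** "opioid-negative urine results and negative self-reported frequency of opioid use since last follow-up".
- **Primary outcome measures:** "opioid abstinence confirmed by negative urine screening and self-report".
- **Description of some major assessments:** "Urine screening for opioids is considered as a gold standard for monitoring abstinence".

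On blinding, **Study setting** begins "Although double blinding will not be possible in the study" and then names treating clinicians, outcome assessors and data analysts as blind. Participants are not named.

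**The concern.** The word abstinence appears to carry two meanings. For the primary outcome, both sources must be negative. For the duration outcome, the only named source is the participant's own recall, and nothing lets a positive strip interrupt a run. The same person could then be non-abstinent on the primary outcome and a perfect abstainer on the secondary one.

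The stake is reporting bias. Participants know whether they are doing yoga or waiting for it. If willingness to admit use differs between the arms, an outcome built on self-report passes that difference into the estimated yoga effect. The urine results that would limit it are already scheduled every month.

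**Working it through.** The plan gives no figure for this outcome, so there is nothing to reproduce. The check compares the text and then works through single records.

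**1. Sources side by side**

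| Outcome | Status | Named source |
|---|---|---|
| Opioid abstinence | Primary | Negative urine and negative self-report |
| Longest continuous abstinence | Secondary | TLFB |

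Clinical assessment and Table 1 agree on the TLFB, so the source is stated twice. No section says how a positive strip changes a TLFB-based run.

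**2. Single records**

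Inputs from the document: 24 weeks of follow-up and monthly urine.

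Assumptions: strips fall at weeks 4, 8, 12, 16, 20 and 24, and a positive strip cancels the b weeks up to and including the sample, with b = 1, 2 or 4. The document gives no look-back window.

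The score is the longest stretch of weeks not cancelled. The participant denies all use in every row.

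| Positive strips | TLFB only | b = 1 | b = 2 | b = 4 |
|---|---|---|---|---|
| None | 24 | 24 | 24 | 24 |
| Week 12 | 24 | 12 | 12 | 12 |
| Weeks 12 and 24 | 24 | 11 | 10 | 8 |
| All six | 24 | 3 | 2 | 0 |

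At the three-month visit, with positives at weeks 4 and 8, TLFB gives 12 weeks. With the strips counted, the longest stretch is weeks 9 to 12, which is 4 weeks under each window.

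The TLFB-only column never moves. In every row with a positive strip, the participant has failed the urine part of the primary definition for that period.

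**3. Illustration of an arm mean (all rates assumed)**

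Suppose half the participants use opioids at some time. Users use in any given week with probability 0.3 or 0.6. A monthly strip detects use in its own week with 90% sensitivity, and b = 1. Simulation then gives these mean longest runs for a user who denies use:

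| Weekly use | True run | TLFB only | TLFB plus urine |
|---|---|---|---|
| 0.3 | 6.8 | 24.0 | 15.6 |
| 0.6 | 3.1 | 24.0 | 10.3 |

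Overstatement of the arm mean = 0.5 × (share of users who deny) × (credited run − true run).

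- TLFB only, 10% deny: 0.5 × 0.10 × (24.0 − 6.8) = 0.86 weeks; 0.5 × 0.10 × (24.0 − 3.1) = 1.05 weeks.
- TLFB only, 30% deny: 0.5 × 0.30 × 17.2 = 2.58 weeks; 0.5 × 0.30 × 20.9 = 3.14 weeks.
- With urine, 10% deny: 0.5 × 0.10 × (15.6 − 6.8) = 0.44 weeks; 0.5 × 0.10 × (10.3 − 3.1) = 0.36 weeks.
- With urine, 30% deny: 0.5 × 0.30 × 8.8 = 1.32 weeks; 0.5 × 0.30 × 7.2 = 1.08 weeks.

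The formula is linear in the share who deny. A 10-point difference in denial between arms would therefore create a spurious difference of about 0.9 to 1.0 week on TLFB alone, and about 0.4 week with the urine rule. These figures show direction and how much a monthly strip can recover. They do not estimate the bias in this trial.

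**The case against.** The strongest reply is that the article names an instrument and does not say that urine is ignored. Abstinence is defined with both parts, and the secondary outcome could be read as keeping that meaning, with the TLFB supplying the week-by-week calendar that a monthly strip cannot. How a positive strip breaks a run, and over what window, is ordinary analysis-plan detail. A self-reported secondary outcome beside a urine-confirmed primary is also defensible, and two outcomes from different sources may disagree without either being wrong. Assessors are blind, and both arms have the same urine schedule and the same assessment payment, so a difference in denial between the arms is conjecture.

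Part of this stands. A reader might infer that the plan prescribes TLFB alone and knowingly credits urine-positive deniers. It does not say so; that follows only from the TLFB being the sole named source and from the lack of a rule for discordant results. An unseen analysis plan could carry the urine condition over. Differential denial is a possibility only.

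A reader might also infer from the separate three- and six-month ticks in Table 1 that runs are cut at month 3, so that 24 abstinent weeks would score 12 and 12. The document does not say this. The ticks show when data are collected, and the outcome is a single longest duration.

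What does not stand is the claim that this is mere silence. The source is named in the text and again in the schedule, and an analysis plan that followed both would use self-report. That choice is weaker than the trial's own definition, and the data for a better one are already being collected.

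**Conclusion.** The point holds as a cheap improvement of minor severity. The only named source for the longest-abstinence outcome is self-report, which does not match the trial's two-part definition of abstinence or its stated gold standard. For a participant who denies use and has positive strips, the direction of the error is certain: the run is too long or, at best, unaffected.

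The size is unknown. The per-record results depend on an assumed strip timing and look-back window. The arm-level figures also depend on assumed rates of use, denial and strip sensitivity, none of which the documents give. They should not be quoted as the bias in this trial.

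The reach is limited to one secondary outcome. It would be wrong to infer that the primary abstinence result is compromised in the same way, because that outcome requires negative urine as well.

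**What to change.** Derive the duration from the TLFB calendar and the scheduled monthly urine results together:

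- A positive scheduled strip ends the run, whatever the self-report, over a look-back window fixed before unblinding.
- Use one continuous calendar from randomisation to week 24, and state this explicitly so that no run is cut at the three-month visit.
- Report the TLFB-only duration as a sensitivity analysis, labelled self-reported.

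The cost is a few lines in the analysis plan and a derivation program; no new data are needed.

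There are two downsides. A false-positive strip shortens a true run, and in a participant abstinent throughout, a single one at week 12 cuts 24 weeks to 12. The TLFB-only sensitivity analysis shows how far this matters. Monthly strips also reduce the bias without removing it: in the illustration a user who denies use is still credited with 15.6 or 10.3 weeks, against true runs of 6.8 or 3.1.

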### Data storage, handling, and statistical analysis

A data monitoring committee (DMC) will be created, which will be chaired by the biostatistician. The DMC will be independent from the sponsor and any competing interests. Data handling, coding and password-protected data storage will be supervised by a biostatistician. The biostatistician will also supervise data anonymization and data analysis. The data will be suitably anonymized so that no identification features are revealed. Data anonymization will be done by the biostatistician creating a mirror image of a database and implementing alteration strategies, such as character shuffling or encryption.

#### Primary outcome measures

Key measures include opioid abstinence confirmed by negative urine screening and self-report, levels of pain measured by BPI, the intensity of craving tracked by OCS, beta-endorphin levels, and fMRI-BOLD responses to tasks (stop signal, visual cue craving) and resting state functional connectivity through fMRI.

#### Secondary outcome measures

These include percentage of participants maintaining abstinence, the longest duration of continuous abstinence, withdrawal symptoms (COWS), severity (CGI), pain threshold (algometer), cognitive performance (n-back task and Stroop task), stress levels (PSS), quality of sleep (PSQI), functioning (WSAS), HRV, cortisol levels, brain GABA levels through MRS, buprenorphine dosage during withdrawal and maintenance phases, side effects (UKU), and gunas (VPI).

### Data analysis

The R programming language will be used to analyze data (R Core Team 2022; 56). Details of dropped-out/withdrawn patients will be recorded. Missing data, drop-outs, non-compliance, and adverse events will be managed in collaboration with the biostatistician and supervisor. The data of all randomized participants will be analyzed using intent-to-treat analysis and mixed model multivariate analysis. Imaging analysis details are provided below. OST/MOUD dosage will be used as a covariate in the analysis. Interim analysis will be done when 50% of the target sample size completes the trial. Information regarding solicited and spontaneously reported adverse events and other unintended effects of trial interventions or trial conduct will be documented and reported to the DMC as well as the ethics committee of the institution. The DMC will have access to interim analysis results and will take the decision to terminate the trial in case of unreasonable morbidities or mortalities among the recruited participants during the trial. Information obtained from the interim analysis may be used for enhancing trial efficiency by updating design and/or sample size adjustments, this will be done as per the suggestions of DMC and after due approval from the funding agency. Trial conduct will be audited once in a year by the DMC, the process will be independent from investigators and the sponsor.

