### Sample size estimation

For evaluating the primary objectives, the optimal sample size was estimated using the principles and methods for the assessment of primary parameters (abstinence, pain, craving, plasma beta-endorphins and fMRI changes). Based on approximation and estimation from the previous data on the clinical effects of yoga interventions in OUD/other patients with substance use disorder supporting a medium effect size^37,40,43,44^, it was estimated that, for an allocation ratio of one, a sample size of at least 82 OUD patients in each arm (accounting for a potential drop-out rate of 36% at six months^40^ with 60 completing the entire study (for the pre- versus post- comparisons of patients) will be required to detect a two-tailed significant difference of α = 0.01 with an estimated 80% power.

The subset sample size of 50 for imaging studies (in each group − pre as well as post-brain scans) will be sufficient to perform random effect analysis for fMRI BOLD changes with multiple comparison correction using random field theory-based family-wise error correction to control for multiple comparison (http://www.fil.ion.ucl.ac.uk/spm/).

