**Pain and Craving Assessment**				
Brief Pain Inventory	✓	✓	✓	✓
Opioid Craving Scale	✓	✓	✓	✓

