**Physiological Measures**				
Plasma Beta-Endorphin Levels	✓		✓	✓
Functional Magnetic Resonance Imaging (visual cue craving task, stop signal task, resting state functional connectivity and MRS)	✓		✓	✓
Heart Rate Variability	✓	✓		
Pressure Algometer (Pain Threshold)	✓	✓	✓	✓
Serum Cortisol	✓		✓	✓

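### The clinical mixed model names OST/MOUD dosage as a covariate but not the Day 0 value of the outcome; if Day 0 enters as an ordinary time point or through change scores, precision is lost on pain, craving and beta-endorphin

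*Protocol article*

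**What the plan says.** The Data analysis section of the protocol article plans an intent-to-treat, multivariate mixed-model analysis of all randomised participants. Its only statement about adjustment is "OST/MOUD dosage will be used as a covariate in the analysis". It gives no list of model terms for the clinical outcomes, does not say that dosage is the sole covariate, and does not say how Day 0 values are used.

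The Primary outcome measures section includes pain, craving and beta-endorphin. In Table 1, "Brief Pain Inventory" and the Opioid Craving Scale are scheduled at Day 0, 15 days, three months and six months. "Plasma Beta-Endorphin Levels" are scheduled at Day 0, three months and six months.

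Two places hint at the role of Day 0:

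- The Sample size estimation section describes the 60 completers as being "for the pre- versus post- comparisons of patients".
- The imaging section (Data Preprocessing and Analysis) contains the only model that is spelled out. There month 0 is one level of the within-subject time factor, alongside months 3 and 6, with arm as the between-subject factor. No equal-baseline constraint is mentioned.

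**The concern.** The section makes a covariate choice for the clinical model, and the choice it makes does not include the pre-randomisation value of the outcome, which is usually among the strongest predictors of the later value. If the clinical model follows the imaging model, or works with pre-to-post differences, the yoga effect becomes a difference in change from Day 0. That contrast carries the full sampling noise of the Day 0 measurement in both arms. Adjusting for Day 0 removes the part of the follow-up variance that Day 0 predicts, without adding that noise.

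What is at stake is precision on three primary outcomes, in a trial that tests at two-sided 0.01 and expects 36% dropout. Validity is not in question.

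**Working it through.** **Inputs from the article (Sample size estimation).** Two-sided alpha 0.01; "with an estimated 80% power"; earlier data "supporting a medium effect size", with no number given; "a sample size of at least 82 OUD patients in each arm"; 36% dropout; 60 completing, read here as per arm.

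**Inputs assumed.** d = 0.5 for a medium effect. Correlation ρ between Day 0 and follow-up of 0.3, 0.5 and 0.7. The article gives neither.

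**The plan's own figure.** For two independent means, n per arm = 2[(z₀.₉₉₅ + z₀.₈)/d]² = 2(2.576 + 0.842)²/0.25 = 93.4, so 94 completers per arm and not 60. With 60 per arm and d = 0.5 the power is 56.5% by the normal approximation (55% by noncentral t). An 80% power with 60 per arm needs d = 3.417 × √(2/60) = 0.624. The stated 80% is therefore not reproduced at d = 0.5, so the comparison is shown at both effect sizes.

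**Variance of the arm difference at one follow-up visit**, relative to comparing follow-up values alone (factor 1):

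- change from Day 0, or a free arm-by-time contrast against Day 0: 2(1 − ρ)
- adjusted for Day 0, or baseline means constrained equal: 1 − ρ²

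The difference is 2(1 − ρ) − (1 − ρ²) = (1 − ρ)², which is positive for every ρ below 1. The change contrast is thus always the less precise of the two. Its relative efficiency is (1 + ρ)/2, that is 0.65, 0.75 and 0.85 at the three correlations.

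**Power, n = 60 per arm, alpha 0.01, d = 0.5 (noncentral t).** The noncentrality is 0.5 × √(60/2) / √factor = 2.739/√factor.

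| ρ | Factor, change | Power, change | Factor, adjusted | Power, adjusted | Gain (points) |
|---|---|---|---|---|---|
| 0.3 | 1.40 | 38.4% | 0.91 | 60.0% | 21.6 |
| 0.5 | 1.00 | 54.9% | 0.75 | 70.6% | 15.7 |
| 0.7 | 0.60 | 81.9% | 0.51 | 88.6% | 6.7 |

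**The same at d = 0.624 (normal approximation)**, where comparing follow-up values alone has the plan's 80%:

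| ρ | Power, change | Power, adjusted | Gain (points) |
|---|---|---|---|
| 0.3 | 62.3% | 84.3% | 22.0 |
| 0.5 | 80.0% | 91.5% | 11.5 |
| 0.7 | 96.7% | 98.6% | 2.0 |

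**Check in a repeated-measures model.** Generalised least squares variances were computed for four visits with compound symmetry, keeping Day 0 as a response. A free arm-by-time contrast gave factors 1.40, 1.00 and 0.60. A common baseline mean gave 0.91, 0.75 and 0.51. These match the formulas, so having Day 0 among the responses does not settle the matter. The equal-mean constraint does.

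**The case against.** The strongest objection is that the article is silent rather than wrong. It is a condensed journal text, the SAP is not shown, and the terms of a mixed model are commonly left to such documents. Most of this stands. A reader might infer that dosage is the only covariate, or that Day 0 values are left out. The text says neither, and the hints it gives point to Day 0 being used in some form. What remains is that the article does publish a covariate choice, and its hints lead towards the less precise form.

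A reader might also infer a comparison of follow-up values alone, with chance baseline differences left in the estimate. No section describes such an analysis. Under randomisation it would in any case be unbiased, as would a change analysis.

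It is also tempting to say that the design does nothing about baseline severity. Eligibility does restrict it: entry requires CGI-S above 3, and patients with intractable pain from other diseases or opioids prescribed for other pain are excluded. These criteria narrow the spread, but they neither balance the arms nor replace adjustment.

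Finally, the power figures rest on an assumed d and ρ, with one ρ applied to three different measures at a single visit. That is correct. No single figure should be quoted as the loss; only the direction is free of these assumptions.

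**Conclusion.** The point holds as a conditional loss of efficiency, not as an error. If Day 0 enters the clinical model as an unconstrained time point or through change scores, the analysis is valid but less precise than a baseline-adjusted one at every correlation below 1. At d = 0.5, 60 completers per arm and two-sided alpha 0.01, adjustment is worth about 22, 16 and 7 power points at ρ = 0.3, 0.5 and 0.7. At d = 0.624 it is worth about 22, 11 and 2. The loss is zero if a common-baseline model is already intended.

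The conclusion covers pain, craving and beta-endorphin. The calculation does not apply to abstinence, which is binary, and was not made for imaging. Two other matters touch the same text but are separate from this point: the sample size does not reproduce at d = 0.5, and the article does not say whether the dosage covariate is the Day 0 dosage or one recorded after randomisation, although buprenorphine dosage is also a secondary outcome.

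**What to change.** In the Data analysis section, add that BPI, OCS and beta-endorphin are analysed with their scheduled post-baseline values as responses (15 days, three and six months for BPI and OCS; three and six months for beta-endorphin). The model has arm, visit and arm-by-visit, adjusted for the Day 0 value of the same outcome and its interaction with visit.

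The equivalent alternative is a longitudinal model that keeps Day 0 as a response, with baseline means constrained equal between arms. It also retains patients whose Day 0 value is missing.

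The cost is one sentence. The Day 0 measurements are already in Table 1, so no new data or patients are needed. If the sponsor already intends either model, the sentence simply records it.
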